## 4 TRIAL DESIGN

### 4.1 Type of Trial and Design

This controlled randomised open labelled phase 1 pharmacokinetic study will be conducted at the MRC ward in the AFPRC hospital in Farafenni, The Gambia as single site. Samples will be analyzed at the MRC Unit, Farafenni and Fajara and at The London School of Hygiene and Tropical Medicine in the UK.

The 90 participants will be randomized into three parallel study groups:

- 30 subjects in Group 1 as control, who will receive artesunate and water
- 30 subjects in Group 2 who will receive AC and artesunate simultaneously
- 30 subjects in Group 3 who will receive AC 1 hour after artesunate.

The study is expected to last 5 months. Subject recruitment and enrolment will last for 3 months. Each subject will stay in hospital for dosing and sample collection for 18 to 24h. The subsequent 2 months will be used to provide health care for study participants.

### 4.2 Randomisation Procedure

90 random numbers will be generated in blocks of 15 (e.g. 1-15, 16-30) using the random numbers generation function from Excel, Microsoft. In order of appearance, at the random numbers generator, these numbers will be allocated to group 1, 2 or 3, respectively, so that after each set of 15 numbers an equal distribution to all three groups is guaranteed. Cards with the group numbers 1-3 will then be put into envelopes labelled with the numbers that have been randomized to each group. The envelopes will then be arranged in ascending order. The envelopes will be allocated one after the other to eligible subjects in the order they are enrolled in the study.

### 4.3 Investigational Product

#### 4.3.1 Artesunate

Artesunate for intravenous injection is manufactured by Guilin Pharmaceutical CO., Ltd, China. It comes as Artesunate acid in vials of 60-mg. The pack also contains a 1ml ampoule of 5% sodium bicarbonate as solvent.

Artesunate will be given to all study participants intravenously at a dose of 2.4mg/kg bodyweight on day 0, and after 12 hours.

## Clinical Trial: Charcoal

---

The vials and ampoules will be stored at room temperature in an air-conditioned room at the study site, with access limited to the investigators only.

### **4.3.2 Activated Charcoal**

Activated charcoal (Aktivkohle, Granulat, 1,5 mm, reinst) is manufactured by Caesar & Loretz GmbH, Germany. It comes as black granules in pre-packaged sachets of 50g.

The 50g AC will be dissolved in 350mls of water and will be given orally to subjects. The granules will be stored at room temperature in an air-conditioned room at the study site, with access limited to the investigators only

## 5 SELECTION AND WITHDRAWAL OF SUBJECTS

### 5.1 Selection of Subjects

The study population will be drawn from the villages in the Farafenni area, Upper River Division, The Gambia. It is planned to approach potential volunteers in the field. The investigators and a team of field workers (FW) will go to the community and explain the study during a sensitisation visit. Villages that are interested in the study will be visited by the FW when the trial is ready to start. The information sheet will be made available to those interested in the study. All persons expressing an interest in participating will be invited for screening for which verbal consent will be obtained.

### 5.2 Eligibility of Subjects

#### **Inclusion Criteria:**

Subjects must meet all of the inclusion criteria listed below in order to be eligible to participate in the trial.

- Healthy Gambian adult aged 21 to 45 years of any tribe of African origin.
- No malaria parasites in the blood (demonstrated by a negative optimal test and confirmed on a thick film)

#### **Exclusion Criteria:**

All subjects meeting any of the exclusion criteria listed below at baseline will be excluded from trial participation.

- Hb < 11g/dl
- Concurrent participation in any other study
- Breastfeeding or pregnant women
- Taken any medications in the past one week

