## **2.3 Potential Risks and Benefits**

The suggested doses of activated charcoal have been derived from official guidelines for treatment of poisoning that recommend 50-100g AC for adults, or 10-25g in children less than 5 years old, respectively. Activated Charcoal will be diluted in 350mls of water.

Oral activated charcoal is an inert, non-toxic drug. It may taste bitter and at higher doses may cause some constipation.

Artesunate will be given intravenously, at a dose of 2.4mg/kg on day 0, and after 12 hours. Mild tenderness, bruising, or fainting may result from venepuncture.

Intravenous artesunate is highly effective in killing malaria parasites and at the suggested dose has an excellent safety profile(13). However, it should be mentioned that in animals intramuscular administration of the oil based artemisinin derivatives artemether or arteether have produced an unusual selective pattern of damage to certain brain stem nuclei, particularly those involved in the auditory relay(17, 18). However, there is no evidence of similar damage in humans. Recent studies of auditory-evoked potentials in Vietnamese and Thai patients treated with artemisinin derivatives have provided reassuringly normal data(19). Moreover, in animal models the water-soluble compounds such as artesunate have given significantly less neurotoxicity than intra-muscular administration of the oil based compounds(20), and in a large cohort treated with either artesunate or artemether there was no evidence of any adverse nervous system effect(21). A recent study further demonstrated that no DHA was detectable in the CSF upon intravenous application of artesunate(22), and an up to date expert review concludes that artemisinin derivatives have no identifiable dose-related adverse effects in humans and only very rarely produce allergic reactions

All 90 study participants will be given an ITN at the end of the study. For a period of 2 months the study participants and their immediate family (wife(s), husband, biological children) will be granted

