**7.2 Trial Evaluations****7.2.1 Clinical Evaluations**

The clinical assessment by the trial physician includes a physical examination to measure weight and the vital signs (axillary body temperature, pulse rate, blood pressure, and respiratory rate). The heart and chest will be auscultated, the liver and spleen will be palpated.

Vital signs will be assessed before application of artesunate and after 12h and 18-24 h.

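### Section 5.2 has no exclusion for known hypersensitivity to artemisinins, although every healthy volunteer is to receive intravenous artesunate twice

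*Protocol*

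**What the plan says.** Section 5.2 of the protocol introduces its exclusions with the rule "All subjects meeting any of the exclusion criteria listed below at baseline will be excluded from trial participation". Four items follow: haemoglobin below 11 g/dl, "Concurrent participation in any other study", "Breastfeeding or pregnant women" and "Taken any medications in the past one week". There are two inclusion criteria: "Healthy Gambian adult aged 21 to 45 years of any tribe of African origin", and absence of malaria parasites.

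On exposure, section 4.3.1 states: "Artesunate will be given to all study participants intravenously at a dose of 2.4mg/kg bodyweight on day 0, and after 12 hours". This covers all three groups, controls included.

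On risk, section 2.3 closes its review of artesunate by citing an expert conclusion that "artemisinin derivatives have no identifiable dose-related adverse effects in humans and only very rarely produce allergic reactions".

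**The concern.** Eligibility criteria should at least cover the harms that the protocol itself attributes to the study drug, where a simple question can identify the people concerned. Here the risk section names one kind of human reaction to the drug class, and the criteria do not address it. Someone who had a recognised reaction to an artemisinin at some time before the past week meets both inclusion criteria and none of the exclusions.

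What is at stake is the safety of a healthy volunteer who has no illness for the drug to treat. Eligibility is protocol content, so a statistical analysis plan would not be expected to settle it.

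**Working it through.** No formula or figure in the plan depends on this point, so the check sets the sections side by side.

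1. **Exclusions (5.2).** Of the four items, none mentions allergy, hypersensitivity or a past drug reaction. The medication item comes closest, but it concerns intake within one week and not how the person reacted to an earlier course. Result: 0 of 4.

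2. **Inclusions (5.2).** Health is required but not defined. A person with a past drug allergy can be entirely healthy, and the parasite criterion is unrelated. Result: 0 of 2.

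3. **Field screening (7.1.1).** The described content is a finger-prick haemoglobin, a malaria antigen test and a thick film, with questions to women about pregnancy, breastfeeding and a missed period. No question about drug reactions is described.

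4. **Enrolment and assessment (7.1.2, 7.2.1).** Enrolment also requires the study physician to judge the subject clinically fit. On content, section 7.2.1 says: "The clinical assessment by the trial physician includes a physical examination to measure weight and the vital signs". It goes on to auscultation of heart and chest and palpation of liver and spleen. None of these findings would reveal a past drug reaction.

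5. **Risk (2.3).** The neurotoxicity signal is attributed to animals, with no evidence of similar damage in humans, and dose-related effects in humans are denied. Constipation and a bitter taste belong to the charcoal; tenderness, bruising and fainting belong to venepuncture. For artemisinins in humans this leaves allergy as the only reaction named.

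6. **Exposure (4.1, 4.3.1).** 90 subjects × 2 doses = 180 planned intravenous doses.

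7. **Size.** The documents give no rate for artemisinin allergy and no figure for earlier artemisinin use in this population. Let p be the share of otherwise eligible volunteers who know of a past reaction. The expected number enrolled is 90 × p, which is below 1 whenever p is below 1/90, about 1.1%. Since section 2.3 calls such reactions very rare, and a volunteer must also have been exposed before and have recognised the reaction, p is assumed to lie well under that value.

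Read together, items 1 to 4 show that applying the written criteria would admit a volunteer with a known reaction. Items 5 and 6 show that the criterion is relevant to every subject.

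**The case against.** The strongest reply is that the written list is not the only barrier. Section 5.2 says who must be excluded; it does not say that nothing else can exclude. Section 7.1.2 adds the fitness judgement, and section 7.2.1 says what the assessment includes, which is not exhaustive wording. The medication and concurrent-study exclusions cannot be applied without asking the volunteer, yet neither 7.1.1 nor 7.2.1 describes those questions. So silence in these sections does not prove that allergy would go unasked. The consent form and case report form, which are not in the text considered here, might also raise it.

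All of this stands, and it rules out one tempting inference: that the protocol obliges the site to enrol an allergic volunteer, or that nobody would ask. What remains is that exclusion would depend on a physician's initiative, because no criterion requires it.

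It is also fair to say that section 2.3 offers its allergy remark as reassurance. A reader might infer that allergy is a prominent or predictable hazard of the drug; the text supports only that it is the one human reaction named for the class.

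Finally, no two sections contradict each other here. The point is a weakness in how the eligibility criteria are drawn, and it is small.

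**Conclusion.** The point holds as a minor participant-safety improvement. Section 5.2 does not exclude known hypersensitivity to a drug given intravenously and twice to every healthy volunteer, although the protocol's own risk section concedes allergic reaction for that class. Under the assumption on p stated above, the expected number affected among 90 is well below one.

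A reader might also infer a threat to the data: sampling begins only after the second dose, dropouts are not replaced (section 5.3), and section 9 omits from the analysis anyone who misses more than one follow-up time. The protocol's own numbers do not support this. Section 9 needs 23 per arm and enrols 30, a margin of 30 − 23 = 7. Its 20% loss allowance is 30 × 0.20 = 6, leaving 24, still above 23. An isolated loss of this kind is immaterial to power and to the pharmacokinetic conclusions, so the case for change rests on safety alone.

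**What to change.** Add one exclusion to section 5.2: known hypersensitivity to artesunate, any artemisinin derivative or a component of the study products. In section 7.1.1, add a question on past reactions to these products beside the existing pregnancy and breastfeeding questions, but put it to all volunteers, men as well as women.

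The cost is one line of criteria and one screening question. The effect on recruitment is negligible, and the sample size, endpoints and analysis are unchanged.

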### 5.3 Withdrawal of Subjects

Subjects may withdraw voluntarily from participation in the study at any time. Subjects may also withdraw voluntarily from receiving the study intervention for any reason. Subjects who dropped out for any reason will not be replaced.

**Clinical Trial: Charcoal**

---

Subjects who withdrew from the trial will be asked to come for a health check to ensure that the participant is in good health.

Subjects who withdrew from the trial due to an adverse event will be followed until resolution of the symptom or laboratory change occurs, or until a non-study related causality is assigned (see Section 7).

## **6 TREATMENT OF SUBJECTS**

There are no restrictions to other medications besides antimalarial treatment before and during the trial.

All study participants will be given an ITN at the end of the study. For a period of 2 months the study participants and their immediate family (wife(s), husband, biological children) will be granted access to the MRC ward at the hospital. A SEN will accompany the screening team and will be equipped to treat minor acute ailments.

## 7 TRIAL PROCEDURES AND EVALUATIONS

### 7.1 Trial Schedule

For an overview see Appendix A: Summary Participant Schedule

#### 7.1.1 Screening

Screening will be performed in the field. It will consist of a finger prick sample to estimate Haemoglobin by (**HemoCue®**) and to look for malaria parasites using Malaria antigen test (**OptiMAL®**). A slide with a thick film will be prepared for microscopic exclusion of malaria parasites. Only slides from those who were found eligible and are willing to participate will be examined on the MRC ward at AFPRC hospital.

All women of child bearing age will be asked if they are pregnant or breastfeeding. Any woman of child bearing age who has missed her last menstrual period will not undergo any of the screening procedures.

For ease of identification, all volunteers will be given a piece of paper with a unique 3-digit screening number on it to enable identification at the hospital. Volunteers that have been found eligible will be invited to the AFPRC hospital either by 7.00 pm the day of screening or by 7.00 pm of the following day.

For the duration of the study volunteers will be treated as inpatients at the MRC ward in the AFPRC hospital. Written informed consent will be obtained prior to a clinical examination performed by the study physician. All women will undergo a pregnancy test and results must be available prior to administration of artesunate.

#### 7.1.2 Enrolment

Eligible volunteers will be enrolled into the study and allocated to one of the three treatment groups according to randomisation (see section 4.2).

The study physician will perform a clinical assessment. Subjects assessed to be clinically fit will be enrolled in the study and allocated to one of the three treatment groups according to randomisation (see section 4.2).

An indwelling forearm catheter will be placed. The first i.v. blood sample will be taken for routine biochemistry, FBC, and a thick film investigation for malaria parasites.

**Clinical Trial: Charcoal**

---

**7.1.3 Follow-up**

A physical examination will be performed after 18-24 hours at discharge. Any adverse event will be followed until resolution of the symptom or laboratory change occurs, or until a non-study related causality is assigned

**7.2 Trial Evaluations****7.2.1 Clinical Evaluations**

The clinical assessment by the trial physician includes a physical examination to measure weight and the vital signs (axillary body temperature, pulse rate, blood pressure, and respiratory rate). The heart and chest will be auscultated, the liver and spleen will be palpated.

Vital signs will be assessed before application of artesunate and after 12h and 18-24 h.

**7.2.2 Laboratory Evaluations**

A routine biochemistry and hematology will be performed before the application of artesunate.

- Biochemistry:  
potassium, sodium, urea, creatinine, total bilirubin, alkaline phosphatase (ALPH), aspartate aminotransferase (AST), albumin.
- Hematology:  
Hemoglobin, hematocrit, white blood cells (WBC) with differential count, platelet count.

Serum creatinine and albumin will be measured in addition at the same time points when the plasma levels of artesunate and DHA will be determined.

**Parasite determination:**

Apart from the (**OptiMAL**® test, the thick blood film prepared in the field will be investigated for malaria parasites by an experienced slide reader before application of artesunate

**Plasma level determination**

Plasma samples will be collected to determine the levels of artesunate and its metabolite DHA as well as para-aminobenzoic acid (PABA) at the time points 5, 10, 15, 30, 60, 90 min and 3 and 6 hours after the second dose of artesunate has been given. Samples will be frozen immediately and stored in LiN2 at the MRC field station nearby, and will be transported on dry ice via Fajara to the London School of Hygiene and Tropical Medicine in the UK. Here, samples will be analyzed by liquid chromatography – mass spectrometry (LC-MS)

## 8 SAFETY CONSIDERATIONS

All adverse events (AE) occurring in participants after administration of one of the investigational products will be recorded and reported as described in the Standard Operating Procedure “Adverse Events (AE) & Serious Adverse Events (SAE)”.

Every AE observed or reported from the day of the first administration of a study drug (Day 0) will be recorded on the Case Report Form (CRF). All AEs will be followed until resolution of the symptom or laboratory change occurs, or until a non-study related causality is assigned.

The investigator will make interpretation of the causal relationship of the adverse event (AE) in question to the intervention.

All serious adverse events (SAEs) will be reported by telephone, email or fax to the local safety monitor, and the Joint Gambian Government/ MRC Ethics Committee within one working day of the investigator becoming aware of the SAE occurrence. The local safety monitor will review SAEs immediately after they occur and follow these events until resolution.

The local safety monitor, who is independent of the trial, will provide real-time safety oversight. The local safety monitor will review the available safety data and may offer guidance on how to proceed.

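### Section 8 allows one working day to report an SAE to the local safety monitor; if that window is used in full, the immediate review and real-time oversight promised there cannot be delivered

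*Protocol*

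**What the plan says.** Protocol Section 8 makes three statements about SAEs that bear on timing.

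- Reports go by telephone, email or fax to the local safety monitor and the Ethics Committee "within one working day of the investigator becoming aware of the SAE occurrence".
- On review: "The local safety monitor will review SAEs immediately after they occur and follow these events until resolution".
- On oversight: "The local safety monitor, who is independent of the trial, will provide real-time safety oversight".

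The monitor's stated power is advisory: this person "may offer guidance on how to proceed". Section 8 also refers to a separate document, since adverse events are to be "recorded and reported as described in the Standard Operating Procedure" on AEs and SAEs. That SOP is not among the documents at hand.

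Three other sections set the timetable against which the reporting window has to be read.

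- Section 7.1.1: eligible volunteers are "invited to the AFPRC hospital either by 7.00 pm the day of screening or by 7.00 pm of the following day". Appendix A places the first dose in the evening of day 0.
- Section 4.3.1: "Artesunate will be given to all study participants intravenously at a dose of 2.4mg/kg bodyweight on day 0, and after 12 hours".
- Section 4.1: "Subject recruitment and enrolment will last for 3 months", for 90 participants in three equal groups.

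The available text does not define a working day, does not limit dosing to particular days of the week, and gives no faster route to the monitor outside office hours.

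**The concern.** The reporting limit and the review promise run on different clocks. The limit starts when the investigator becomes aware and is counted in working days. The review promise starts when the event occurs and allows no delay. The monitor depends on the investigator's report, so an investigator who complies fully with the first rule can make the second undeliverable.

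The evening start gives this practical weight. The first 12 h after dosing run overnight, so an event in that period becomes known outside office hours, when a working-day clock is at its slowest. Before a weekend or public holiday the permitted delay becomes long.

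At stake is how soon the independent reviewer named in Section 8 learns of a serious event in healthy volunteers. Section 2.2 says the interaction between artesunate and oral charcoal has not been studied before. The trial's estimates and tests are not at stake.

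**Working it through.** The plan gives no figure to reproduce, so the check is a comparison of the rules followed by calendar arithmetic.

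**Inputs from the protocol.** Reporting limit of one working day from awareness (Section 8); arrival by 7 pm (Section 7.1.1) and first dose that evening (Appendix A); second dose 12 h later (Section 4.3.1); 90 subjects enrolled over 3 months (Section 4.1).

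**Assumptions.** The investigator becomes aware at 19:00; a later hour shortens each gap by the same amount. The same clock time stands in for the evening dose. The working week is Monday to Friday, with Saturday as a working day shown as the alternative. The window is read as closing at 09:00, 17:00 or midnight on the next working day. Three months is 13 weeks, which is 91 days or 65 weekdays.

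**Step 1: can the rules coexist?** Yes, if the report is made at once. Not if the window is used in full: review cannot come before the report, and the report may properly arrive up to one working day after awareness.

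**Step 2: length of the permitted gap.** From 19:00 to 09:00, 17:00 and midnight of the following day is 14, 22 and 29 h. From Friday evening to Monday adds 48 h.

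| Case | Closes 09:00 | Closes 17:00 | Closes midnight |
|---|---|---|---|
| Ordinary weekday evening | 14 h | 22 h | 29 h |
| Friday evening, Saturday a working day | 14 h | 22 h | 29 h |
| Friday evening, Monday-to-Friday week | 14 + 48 = 62 h | 22 + 48 = 70 h | 29 + 48 = 77 h |

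With the window closing at 17:00, the comparison is 70 h over a weekend against 22 h otherwise. A public holiday would lengthen it further.

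**Step 3: second doses inside the window.** A first dose at about 19:00 puts the second at about 07:00 next morning, 12 h later. Every gap in the table exceeds 12 h. Volunteers admitted on the same evening could therefore have their second dose before the monitor need be told, on any day of the week. This needs no assumption about weekend dosing.

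**Step 4: new volunteers inside a Friday-to-Monday window.** Average intake is 90 / 91 = 0.99 per day with seven-day dosing, or 90 / 65 = 1.38 per day with weekday dosing only.

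- Seven-day dosing, window closing Monday 09:00 or 17:00: the Saturday and Sunday evenings fall inside, 2 x 0.99 = 2.0.
- Seven-day dosing, window closing Monday midnight: Monday evening is added, 3 x 0.99 = 3.0, of whom 2/3 x 3.0 = 2.0 would be in a charcoal group.
- Weekday dosing only, window closing Monday 09:00 or 17:00: none.
- Weekday dosing only, window closing Monday midnight: Monday evening only, 1.4.

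The range is 0 to about 3 at an average rate of intake.

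**Step 5: what a 24 h clock limit would change.** Awareness at 19:00 on Friday would mean a report by 19:00 on Saturday. That is 62 - 24 = 38 h to 77 - 24 = 53 h sooner than the weekend maximum. On an ordinary weekday 24 h is about the same as the present 22 h. The second dose at about 07:00 would still fall before the limit.

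**The case against.** The strongest reply is that Section 8 sets a maximum, not a target. Telephone is the first route it names, and an investigator who calls promptly meets every statement in the section. A reader might infer that the two rules can never both be met; the text does not support that. The promise fails only when the window is used.

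Second, the cited SOP may set a shorter time or an out-of-hours procedure, and the key-roles and contact pages are not in the public copy. This is a fair limit on the finding. It does not remove it, because a stricter SOP would then disagree with Section 8.

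Third, a reader might infer that the local safety monitor is the trial's only independent safety oversight. That goes too far. Every SAE also goes to the Ethics Committee, and Section 10 gives that committee access for reviewing safety. However, the committee is informed on the same clock, so it provides no quicker route.

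Fourth, a reader might infer that an unreported event goes unmanaged, or that several more volunteers would be dosed. Neither follows. Volunteers are inpatients, a physician assesses each one at 12 h and before discharge (Appendix A), and the investigator may act against an immediate hazard without prior approval (Section 13, Protocol Deviations). The monitor's role is advisory, so nothing shows that an earlier call would have prevented a dose. The number of new volunteers can be zero, and the weekend gap assumes a Monday-to-Friday week.

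Fifth, the evening start does not put all early events outside office hours. The second dose and the eight timed samples run from 12 h to 18 h, which is daytime after an evening start. Sections 2.2 and 2.3 also describe both products as having good safety records, so SAEs should be rare.

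These replies narrow the point to a wording conflict with a limited practical consequence. They do not reconcile the two clocks.

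**Conclusion.** The concern holds as a minor inconsistency in safety reporting. If the investigator uses the full window that Section 8 allows, the monitor cannot give the prompt review and real-time oversight that the same section promises, and no available text supplies a faster route.

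The longest ordinary gap is about 62 to 77 h for an SAE known on Friday evening, if the working week is Monday to Friday. It is about 22 h on other days or if Saturday counts. Second doses of volunteers admitted the same evening can fall inside either gap. New admissions inside the weekend gap range from 0 to about 3, depending on weekend dosing, which the protocol neither schedules nor rules out.

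The conclusion is conditional on the unseen SOP not already setting a shorter time. It has no effect on endpoints, analysis or sample size.

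**What to change.** Change Section 8 in three places and bring the SOP into line.

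1. State the limit for reporting to the local safety monitor in clock hours from awareness, for example 24 h, by telephone, on any day of the week. Keep one working day for the Ethics Committee.
2. Tie the monitor's review to receipt: *immediately on receipt of the report*, in place of a time counted from occurrence.
3. Check that the real-time oversight statement still describes what the revised timing can deliver.
4. Confirm that the AE and SAE SOP gives the same limits.

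The second change removes the literal conflict. The first gives the practical gain, which comes at weekends and on holidays; on an ordinary weekday it changes little. A 24 h limit does not guarantee review before a 12 h second dose, so the reporting text should be reconciled with the dosing timetable. No dosing or stopping rule is proposed here.

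The cost is a short amendment and an out-of-hours telephone arrangement with the monitor already provided for. With 90 healthy volunteers and SAEs expected to be rare, the added burden should be slight.
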